##### Clinical pregnancy, ectopic pregnancy, miscarriage and live birth

This will be analyzed at 24 months follow-up postoperatively. If necessary, extend with 9 months to allow full follow-up of pregnancies until delivery.

Kaplan-Meier estimates will be used and comparisons will be based on stratified log-rank tests.

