#### 4.5 Patient drop out/end of study

If a patient becomes pregnant (clinical pregnancy) within 3 months postoperatively:

- drop-out of the study for primary outcome (data cannot be included for primary outcome studied)
- follow up of the pregnancy outcome

If a patient is pregnant (clinical pregnancy) after 3 months postoperatively:

- data can still be included for the primary outcome studied
- secondary outcomes can be studied until drop out
- follow up of the pregnancy outcome

AMH measurements only outside pregnancy.

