### 6.3.2 Time requirements

Patient recruitment will start after approval by the ethics committee. Estimated inclusion time of 60 months (initially estimated inclusion time of 24 months, due to the COVID-19 pandemic important delay in recruitment for which extension of inclusion time with another 36 months).

Primary outcome will be analyzed at 3 months follow-up postoperatively. Secondary outcomes will be analyzed at 24 months follow-up postoperatively. If necessary, extend with 9 months to allow full follow-up of pregnancies until delivery.

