### 6.3.3 Trial monitoring and patient visits

All patients will be seen by the principal/subinvestigators or by one of his/her staff members at the following moment:

- Screening = standard of care  
     Consultation for discussion of the standard preoperative examination, study information will be given if patient is eligible for inclusion.  
     AMH value = standard of care for patients planned for laparoscopic surgery for an endometriotic cyst (part of the screening process)
- Baseline = study visit (can be combined with screening)  
     Completion of the informed consent forms
- Elective hospitalization for surgery = standard of care  
     Randomization  
     AMH value = study sample
- 3 months postoperatively (visit window: minimally 3 months postoperatively + 2 weeks)  
     Visit with postoperative checkup, complications assessment using the Clavien-Dindo classification, anamnesis concerning pain and child wish and transvaginal ultrasound = standard of care  
     AMH value = standard of care
- 6 months postoperatively (+/- 2 weeks)  
     Visit with anamnesis concerning pain and child wish and transvaginal ultrasound = standard of care  
     AMH value = study sample
- 12 months postoperatively (+/- 2 weeks)  
     Visit with anamnesis concerning pain and child wish and transvaginal ultrasound = standard of care

AMH value = study sample

- 24 months postoperatively (+/- 2 weeks)

Visit with anamnesis concerning pain and child wish and transvaginal ultrasound = standard of care

| Procedures                                | Visits    |           |                 |           |          |           |           |
|-------------------------------------------|-----------|-----------|-----------------|-----------|----------|-----------|-----------|
|                                           | Screening | Baseline* | Hospitalization | Follow up |          |           |           |
|                                           |           |           |                 | 3 months  | 6 months | 12 months | 24 months |
| History/clinical exam                     | x         |           |                 |           |          |           |           |
| Informed consent                          |           | x         |                 |           |          |           |           |
| Eligibility assessment                    |           | x         |                 |           |          |           |           |

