##### Cyst recurrence rate

Cumulative recurrences until 24 months postoperatively will be visualised using Kaplan-Meier estimates and compared using stratified log-rank tests (stratified on centre).

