#### **8.6 Timing of data analysis**

Analysis on the primary outcome will be performed when all included patients had their first postoperative blood sample of AMH (3 months postoperatively).

All other analyses after 24 months of follow up (recurrence rate, pregnancy rate,...), if necessary extend with 9 months to allow full follow-up of pregnancies until delivery.

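### Live birth is analysed by Kaplan-Meier with a pregnancy-driven 9-month extension and no fixed horizon; if non-pregnant women are censored at month 24, as the visit schedule implies, the curve greatly overstates the live-birth rate

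*Protocol*

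**What the plan says.** Section 8.4 treats four pregnancy outcomes together. It fixes the time of analysis ("This will be analyzed at 24 months follow-up postoperatively"), allows more time ("If necessary, extend with 9 months to allow full follow-up of pregnancies until delivery") and names the method ("Kaplan-Meier estimates will be used and comparisons will be based on stratified log-rank tests"). Section 8.6 repeats the extension ("if necessary extend with 9 months to allow full follow-up of pregnancies until delivery"), and section 6.3.2 has it too, after stating "Secondary outcomes will be analyzed at 24 months follow-up postoperatively".

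Three other places bear on how this would be carried out:

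- Section 6.3.3 and its visit table end at month 24 for every woman. Nothing is scheduled later.
- Section 4.5 provides for "follow up of the pregnancy outcome", and only for women who become pregnant.
- The recurrence paragraph of 8.4 does carry a limit: "Cumulative recurrences until 24 months postoperatively will be visualised using Kaplan-Meier estimates". The pregnancy paragraph has no matching limit for its curve.

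The protocol gives no event date, time axis or censoring rule for live birth.

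**The concern.** Kaplan-Meier needs censoring that is unrelated to the coming event. The only reason given for observing anyone after month 24 is that she is pregnant. With a delivery-dated event and the stated visit schedule, a routine program would censor each non-pregnant woman at her month-24 visit and keep each pregnant woman until delivery. Between months 24 and 33 (24 + 9) everyone at risk would then be pregnant and most would be about to have the event. Each delivery would remove a large share of a very small risk set, and the product-limit estimate would apply that share to all the women censored at month 24.

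At stake is a published live-birth rate several times too high. The log-rank terms after month 24 would also compare pregnant women only with other pregnant women.

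**Working it through.** **Inputs.** The protocol states no figure for live birth, so there is none to reproduce. The arm size comes from section 8.1: 82/(1 − 0.10) = 91.1, taken to 92 in total, or 46 per arm. Conception and live-birth rates are not in the protocol; all those below are assumptions.

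**Hand example.** One arm of 46, nobody lost before month 24. Nine women deliver by month 24. Five are pregnant at month 24, of whom four deliver and one loses the pregnancy.

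True proportion with a live birth from a conception by month 24: (9 + 4)/46 = 13/46 = 28.3%.

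Kaplan-Meier, S = product of (1 − d/n) over event times:

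1. To month 24: S = 37/46 = 0.804, so the curve reads 19.6%.
2. At month 24 the 37 − 5 = 32 non-pregnant women are censored. With the loss kept at risk to the end, the later risk sets are 5, 4, 3, 2, with one delivery at each.
3. S = 0.804 × (4/5)(3/4)(2/3)(1/2) = 0.804 × 0.2 = 0.161, so the curve ends at 83.9%.
4. If the loss is censored before the first of these deliveries, the risk sets are 4, 3, 2, 1, S falls to 0 and the curve ends at 100%.

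The same data under other rules:

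- Delivery-dated curve stopped at month 24: 9/46 = 19.6%, which leaves out 4 of the 13 births.
- Non-pregnant women and the loss kept at risk as event-free: S = (37/46)(36/37)(35/36)(34/35)(33/34) = 33/46, so 28.3%.
- Event dated at the conception that led to the birth, all other women censored at month 24: 13/46 = 28.3%.

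**Simulation.** 46 women per arm, 1,000 runs per scenario. First conception has a constant hazard set so that 20%, 40% or 60% conceive by month 24; 70%, 80% or 90% of pregnancies end in live birth; delivery is about 9 months after conception and loss at 2 to 3 months. Three of the nine scenarios, as averages over runs:

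| Conceive by month 24 / live birth per pregnancy | True | Non-pregnant censored at 24, losses after 24 censored | Same, losses after 24 kept at risk | Delivery curve stopped at 24 |
|---|---|---|---|---|
| 20% / 70% | 14.1% | 91.8% | 85.9% | 9.2% |
| 40% / 80% | 31.7% | 99.1% | 94.3% | 21.8% |
| 60% / 90% | 54.4% | 99.9% | 98.3% | 39.4% |

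The top and bottom rows give the extremes over all nine scenarios. In the middle row about 4.9 of 46 women are pregnant at month 24, and the first censoring rule takes the curve to 100% in 98.6% of runs. In every scenario, dating the event at conception and keeping all women at risk both returned the true proportion.

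**The case against.** The strongest reply is that the harmful rule is not written down. No section says that the extension is confined to women pregnant at month 24, that the others are censored there, that the event is dated at delivery, or that the curve is read to month 33. The overstatement needs all four. Sections 6.3.2 and 8.6 can be read as saying only when the analysis is run, with the extra months used to learn how existing pregnancies ended, which would be sound. Event dates and censoring rules are also often left to a statistical analysis plan, which may exist here.

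Much of this stands. A reader might infer that the protocol itself prescribes the 84% calculation; it does not, and the point has to be conditional. What remains is that the protocol itself pairs Kaplan-Meier with an extension whose sole stated purpose is pregnancies, schedules no later contact for other women, and gives recurrence a limit that it does not give live birth. The ordinary execution of that text is the biased one. The simplest escape, cutting a delivery-dated curve at month 24, defeats the extension's purpose.

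Three further inferences are tempting but unsupported:

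- *That miscarriage and ectopic pregnancy must be handled as terminal competing events.* They end a pregnancy, not a woman's chance of a later live birth within 24 months. Keeping her at risk for a first live birth is legitimate, and the protocol does not say that she is censored.
- *That log-rank power falls by a known amount.* The protocol gives no conception rate and no expected difference between arms, and the direction of the change varied with the assumed rates.
- *That the trial's main result is threatened.* It is not: the primary outcome is AMH at 3 months.

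**Conclusion.** The concern holds in conditional form. If non-pregnant women are censored at month 24 and pregnant women are followed to delivery, the live-birth curve after month 24 is not interpretable. It reads 84% against 28% in the hand example. Across the simulated scenarios it averages 86% to 98%, or 92% to 100% if later losses are censored, against true values of 14% to 54%. A delivery-dated curve stopped at month 24 understates instead (9% to 39% against the same true values). The exact sizes rest on assumed conception and live-birth rates, but the overstatement was gross in all nine scenarios. Live birth is one of several secondary endpoints, and the AMH analysis and the sample size of 92 are untouched. It should be corrected before the secondary analyses, but it is not a defect that the trial's main conclusion depends on.

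**What to change.** In section 8.4, define live birth as one resulting from a conception within 24 months of surgery. Analyse it per randomised woman in one of two ways:

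- as a proportion, compared between arms with stratification by centre; or
- as time from surgery to the conception that led to the live birth, by Kaplan-Meier and the centre-stratified log-rank test, with all women censored administratively at 24 months.

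State that the 9-month extension serves only to classify the outcome of pregnancies conceived within the 24 months and adds no time at risk. Align the extension sentences in 6.3.2 and 8.6 with this.

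The cost is one paragraph in 8.4 (or in the analysis plan) and two small wording changes. No extra visits, patients or data are needed: the pregnancy outcomes are already to be followed, and the proportion needs no event date beyond knowing that conception fell within the window.

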### **4.2 Inclusion criteria**

In order to be eligible to participate in this study, a subject must meet all of the following criteria:

- Age: 18 – 40 years (both inclusive)
- Unilateral endometriotic cysts with a mean diameter of  $\geq 2.5$ cm and  $\leq 8$  cm, measured in 3 dimensions.
- Presence of a contralateral endometrioma of  $\leq 2$ cm is allowed
- Complaining of infertility and/or pain
- BMI  $\leq 35$
- Use of contraception OCP? (combined or Progesteron only) for at least 4 weeks before surgery

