## 5. TREATMENT OF SUBJECTS

### 5.1 Investigational treatment

Comparison between 2 different laparoscopic techniques in conservative surgical treatment of endometriomas (both arms are existing and accepted surgical strategies):

- Group 1: the combined technique: first step consisting of stripping the cyst wall for 80% of the surface, followed by a second step consisting of ablation of the remaining 20% cyst surface attached to the ovarian vascular hilus and left on site (4)
- Group 2: CO2 laser vaporization only of the complete inner cystic wall after drainage of the cyst content, irrigation and inspection of its inner wall. A biopsy of the cyst wall was

sent for routine histologic examination to confirm the diagnosis of endometriosis. Ablation of the entire inner surface of the cyst wall using the CO2 laser (Lumenis). Power settings of 30–55 W for CO2 laser beam and 6–10 W for CO2 fibre (based on animal data) are usually used. The laser should be on the ablate function to widen the beam (e.g. 'Surgitouch modus'). The laser should be applied in Surgitouch mode so that it can ablate the cyst surface while preserving the underlying healthy tissue. (19)

Intention to treat analysis. Cross over is allowed from group 1 (combined technique) to group 2 (CO2 laser vaporization) if stripping of 80% of the cyst wall is not possible.

If a small contralateral endometrioma is present ( $\leq 2\text{cm}$ ) this will be treated by CO2 laser vaporization only (independent of randomization).

Simultaneous treatment of all visual endometriosis lesions (standard procedure). Operative techniques should be recorded as recommended by the CORDES statement (20).

All patients included in the study undergo surgery after administration of hormonal contraceptives (standard of care). After consultation of all participating centers the decision was made of using oral contraceptives during minimally 4 weeks preoperatively. Use of GnRH agonist is an exclusion criterium since we cannot predict the effect on AMH values. If no child wish was present, advise was given to continue the oral contraceptives postoperatively.

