### 6.1.3 Other study parameters

#### Baseline data:

- age of the participant
- use of contraception + type
- smoking
- previous surgery for ovarian cysts
  - laparoscopy
  - laparotomy
- previous surgery for endometriosis
  - number of surgeries
- indication for surgery:
  - pain
  - Infertility
- pain pattern (+NRS for each parameter)
  - dysmenorrhea
  - chronic pelvic pain/non menstrual pelvic pain
  - dyspareunia
  - dyschezia
  - dysuria
- infertility:
  - duration of infertility
  - primary or secondary infertility
- gravida/para
- BMI (kg/m^2)
- Number of endometriomas
- Diameter of all the cysts (measured in 3 orthogonal planes in mm)
  - Cyst 1
  - Cyst 2
  - ...
- Cyst wall surface
- Uni or bilateral endometriomas
- Baseline AMH value

Surgical data:

- Total Operative time (min)
- Operative time for endometrioma (min)
- Hemostatic method used to manage the bleeding on each ovary
  - Not required (no bleeding)
  - Selective bipolar coagulation + hemostatic device used + power settings
  - Suturing
  - Hemostatic sealants
- rASRM points and stage
- EFI
- Hospital stay (days)
- Follow up (months)
- Complications until 3 months postoperatively as defined by the Clavien-Dindo classification (21)

Postoperative follow-up:

- Baseline questionnaire concerning pain pattern (+NRS for each parameter) at 3, 6, 12 and 24 months follow up
  - dysmenorrhea
  - chronic pelvic pain/non menstrual pelvic pain
  - dyspareunia
  - dyschezia
  - dysuria
- Child wish, if present report management in past period (at 3, 6, 12 and 24 months follow up):
  - Non-ART management:
    - Spontaneously +/- ovulation induction
    - IUI
  - ART management:
    - IVF
    - ICSI
    - Egg donation
- Transvaginal ultrasound (at 3, 6, 12 and 24 months follow up)
- AMH value at 3\*, 6 and 12 postoperatively (\*standard care)

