## 8.2 Baseline data:

|                                                                                                                                                                                                        |                                                         |
|--------------------------------------------------------------------------------------------------------------------------------------------------------------------------------------------------------|---------------------------------------------------------|
| Age of the patient                                                                                                                                                                                     | Continuous                                              |
| Use of contraception                                                                                                                                                                                   | Categorical                                             |
| Smoking                                                                                                                                                                                                | Dichotomous                                             |
| Previous surgery for ovarian cysts 
 
- Number of surgeries
 
- Laparoscopy
 
- Laparotomy
 
                                                | Dichotomous
Continuous
Dichotomous
Dichotomous |
| Indication for surgery: pain and/or infertility                                                                                                                                                        | Categorical                                             |
| Pain pattern (+NRS for each parameter): 
 
- Dysmenorrhea
 
- Chronic pelvic pain
 
- Dyspareunia
 
- Dyschezia
 
- Dysuria
 
 | Continuous                                              |
| Infertility 
 
- Duration
 
- Primary or secondary
 
                                                                                               | Continuous
Dichotomous                               |

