### **8.3 Primary study parameter(s)**

Evaluation of serum AMH at 3 months follow up.

It concerns an intention to treat analysis. All participants will be included in the analysis in the groups to which they were originally assigned, regardless of what subsequently occurred.

To handle the presence of missing values (due to dropout or to pregnancy, in the latter case AMH values after pregnancy are put on missing), a constrained longitudinal data analysis (cLDA, cfr Liang and Zeger, 2010) will be used instead of an ANCOVA to evaluate the differences between the groups in the final analysis. In this approach both the baseline and post-baseline values are modeled as dependent variables, as opposed to a longitudinal ANCOVA model in which the baseline value is included as a covariate. Although the baseline measure is included in the response vector in cLDA, the true baseline means are constrained to be the same for different treatment groups due to randomization, and this analysis provides an adjustment for the observed baseline difference in estimating the treatment effects. Center will be added as a factor in the model. A (logarithmic) transformation of the AMH will be considered to obtain a more symmetric distribution of the model residuals. Using a direct likelihood approach for the cLDA model, a subject with a missing measurement at three months is not excluded from the analysis. As such, the analysis does not assume missing completely at random (MCAR), but is still valid under missing at random (MAR).

References: Liang, K. Y. and Zeger, S. (2000). Longitudinal data analysis of continuous and discrete responses for pre-post designs. *Sankhya: The Indian Journal of Statistics, Series B* 62, 134–148.

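### Pregnancy and live-birth comparisons name no restriction and so read as covering women not trying to conceive; child wish is not recorded before randomisation, leaving only an imperfect baseline proxy for restricting them

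*Protocol*

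**What the plan says.** The protocol plans the fertility outcomes in section 8.4. On timing: "This will be analyzed at 24 months follow-up postoperatively. If necessary, extend with 9 months to allow full follow-up of pregnancies until delivery". On method: "Kaplan-Meier estimates will be used and comparisons will be based on stratified log-rank tests". It does not say which women enter these curves.

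The population rule has to be taken from elsewhere. Section 5.1 states, without limiting it to one outcome, "Intention to treat analysis". Section 8.3, under the primary parameter, adds: "All participants will be included in the analysis in the groups to which they were originally assigned, regardless of what subsequently occurred".

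Two passages show that part of the trial population will not be trying to conceive. Section 4.2 admits women "Complaining of infertility and/or pain", so pain alone is enough. Section 5.1 records the postoperative advice: "If no child wish was present, advise was given to continue the oral contraceptives postoperatively".

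Section 6.1.3 places child wish in the postoperative follow-up list: "Child wish, if present report management in past period (at 3, 6, 12 and 24 months follow up". It is in neither baseline list (6.1.3 and 8.2), and the visit descriptions in 6.3.3 mention it only from the 3-month visit. The baseline table does hold "Indication for surgery: pain and/or infertility", together with the duration and type of infertility. Section 8.5 plans a subgroup by whether contraception is continued after surgery.

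**The concern.** Pregnancy rate is one of the secondary outcomes named in the protocol summary. A woman who continues contraception for 24 months stays in the risk set but has almost no chance of the event. A curve over all randomised women therefore mixes fertility after surgery with the decision to try for a child, and a finding of no difference would be hard to read.

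A statistical analysis plan can define an analysis set, but it cannot create a baseline variable that was never collected. Child wish first asked at 3 months is measured after surgery, when neither surgeon nor patient is blinded (section 6.2). Restricting on it would give up the protection of randomisation. The same is true of the contraception subgroup in 8.5.

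**Working it through.** **The plan's own figure.** The protocol gives no power figure for pregnancy; its sample size rests on AMH (section 8.1). That size reproduces. The difference is 0.30 × 1.9 = 0.57 ng/mL with SD 0.9. The two-sample t-test at two-sided 5% and 80% power needs 40.1, so 41 per arm (82 in total), and 82 / 0.9 = 91.1, so 92, or 46 per arm. I use 46 per arm below.

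**Assumptions not in the documents.** Let f be the share with child wish, and p1 and p2 the 24-month pregnancy risks in the two arms among those women. Women without child wish have no pregnancies. Hazards are exponential, f is equal in both arms, and all women are followed for 24 months. Stratification is ignored.

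**Formulas.**
- Risk over all randomised women: q = f × p, so the difference is f × (p2 − p1).
- Hazard ratio from cumulative risks: HR = ln(1 − p2) / ln(1 − p1), with q in place of p for all women.
- Expected events: 46 × (q1 + q2). This is the same in both sets, because the women removed have no events.
- Schoenfeld power: Φ(|ln HR| × √events / 2 − 1.96).

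**40% v 70%, f = 50%.** Over all women the risks are 20% and 35%, a difference of 15 points instead of 30. Events: 46 × 0.55 = 25.3. Over all women HR = ln(0.65)/ln(0.80) = 1.93, and power = Φ(0.658 × 5.03 / 2 − 1.96) = Φ(−0.31) = 38%. In women with child wish HR = ln(0.30)/ln(0.60) = 2.36, and power = Φ(0.857 × 5.03 / 2 − 1.96) = Φ(0.20) = 58%. Simulation under the same assumptions gives 37% and about 57%.

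**40% v 60%, f = 50%.** The risks over all women are 20% and 30%, with 46 × 0.50 = 23 events. HR is 1.60 over all women and 1.79 in women with child wish; power is 20% and 29%.

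**Range (Schoenfeld).**

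| Risks with child wish | f | Difference, all women | Power, all women | Power, child wish only |
|---|---|---|---|---|
| 40% v 60% | 100% | 20 points | 51% | 51% |
| 40% v 60% | 75% | 15 points | 33% | 40% |
| 40% v 60% | 50% | 10 points | 20% | 29% |
| 40% v 60% | 33% | 6.6 points | 14% | 21% |
| 30% v 60% | 50% | 15 points | 43% | 57% |
| 50% v 70% | 50% | 10 points | 18% | 31% |

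**Does the result depend on zero pregnancies without child wish?** Suppose 10% of those women conceive in each arm. For 40% v 70% and f = 50%, the risks over all women are 0.5 × 40% + 0.5 × 10% = 25% and 0.5 × 70% + 0.5 × 10% = 40%. Then HR = ln(0.60)/ln(0.75) = 1.78, events = 46 × 0.65 = 29.9, and power = Φ(0.574 × 5.47 / 2 − 1.96) = 35%, against 58% in women with child wish. The loss remains.

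**The case against.** **The all-randomised analysis is inferred.** Section 8.4 is silent on the population, the explicit sentence on all participants sits under the primary parameter, and an analysis plan that is not shown may define the set. This stands, and the point is worded accordingly. It does not remove the data gap, because a later plan can use only what was collected.

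**A baseline restriction already exists.** A reader might infer that no restriction is possible without using a post-randomisation variable. The documents do not support that: infertility as the indication, with its duration and type, is recorded at baseline. Section 10.1 also lists the patient's medical file as a source, and the contraceptive advice in 5.1 presupposes that the clinician asks about child wish, although the protocol does not say when. What remains is that infertility as indication is a different variable and leaves out women operated on for pain who also want a child.

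**The intention-to-treat contrast is legitimate.** It is. A reader might infer a biased or invalid test; randomisation protects the type I error. The cost lies in attenuation, power and interpretation.

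**The magnitude is assumed, and restriction does not rescue power.** Both are correct. At f = 50%, every restricted power shown is below 80%.

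**Egg donation.** A reader might add that donor-egg conceptions distort the result because they do not reflect the operated ovary. Section 6.1.3 records egg donation at each follow-up visit, the clinical pregnancy definition quoted in the protocol does not exclude it, and no frequency is given. It can be handled from the recorded data and is no part of this point.

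**Conclusion.** The point holds for a secondary outcome and does not touch the primary AMH analysis. As written, the pregnancy and live-birth comparisons carry no restriction and, under the general intention-to-treat statement, read as covering all randomised women. Child wish, the variable that would define the relevant women, is absent from the baseline data, so the only restriction available from the listed baseline variables is the infertility proxy.

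The direction follows from arithmetic: the difference over all women is about f times that among women with child wish. The size is illustrative. With half having child wish, the assumed scenarios lose about 9 to 20 percentage points of power (29% to 20% for 40% v 60%; about 57% to 37% for 40% v 70%). The figures rest on assumed pregnancy rates, an assumed share, a child wish fixed for 24 months, and few or no pregnancies among the other women.

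**What to change.** 1. Add child wish at randomisation (yes/no) to the baseline data in 6.1.3 and 8.2. For women already enrolled, take it from the preoperative record or, failing that, use infertility as the indication.
2. In 8.4, make women with child wish at baseline the analysis set for clinical pregnancy and live birth, and report all randomised women alongside.
3. State that the 8.5 subgroup by postoperative contraception is not to serve as the restriction for these outcomes, because it is defined after randomisation.

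The cost is one eCRF field, a look back through existing records, and a few lines in 6.1.3, 8.2 and 8.4. The set is smaller and omits women whose child wish arises during follow-up; the all-randomised report still covers them. The comparison remains underpowered and should be presented by its estimate and confidence interval.
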